### Quasi-Experimental Field Study

A randomized controlled trial is generally considered as the gold standard in evaluative health-related research, as causal inferences about the therapy under study can be drawn [27]. However, in this project, there are several practical and ethical issues that do not allow for such a design. Most importantly, a precondition set by the participating organization was that their management would select 2 preexisting departmental units for the study and that both units would receive the intervention. However, a control group is needed to distinguish between the change in the outcome over time due to the planned intervention or to evaluate the changes over time due to unmeasured or unknown factors [27]. Therefore, this study was designed as a quasi-experimental field study with a waiting list control group and pretest-posttest design. This means that one part of the experimental group (ie, unit A) will receive the intervention first, while another part of the group (ie, unit B) waits for an additional 3 months before they can make use of the intervention. Thus, the second unit acts as a temporary control group.

Three types of research methods can be distinguished in this study: (1) a longitudinal web-based survey study, (2) an ecological momentary assessment (EMA) study, and (3) a process evaluation. After the baseline measures (T0) of the web-based survey study are recorded, the yet-to-be-developed intervention aimed at recovery during work will be implemented within the experimental group.

Figure 1 presents a flowchart of the study design and the measurement moments. To analyze the effectiveness of the intervention, follow-up measurements will be performed at 3 months (T1) and at 6 months (T2) after the implementation of the intervention. This timeline seems adequate as the primary study outcomes (recovery during work and short-term negative effects of shift work) are expected to change over a relatively short period of time. In addition, an EMA study will be carried out shortly after the implementation of the intervention to provide insight into the short-term within-person intervention effects. Finally, a process evaluation will be performed to determine the factors that may have either enhanced or mitigated the effectiveness of the intervention.

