### Setting and Study Population

This study is performed at the logistics department of a multinational steel company. This department consists of 160 employees in rotating shift work who are predominantly men, and they are divided into 2 units. These units do not share physical workspaces and are managed separately, thereby minimizing the chance of potential crossover effects. With respect to the demographics and the workload, the units are highly comparable. The typical job positions in both the units are machine operators and logistics coordinators. Open air working conditions are limited for both the participating units. One of the units will be selected to serve as the waiting list control group. This selection will be made in close consultation with the management, considering factors such as organizational planning, expected availability of time, and resources available for each unit.

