4. Safety and performance: Safety and performance at work will be assessed with a self-constructed item for each type of shift (ie, morning/evening/night). A sample item is as follows: “Given the current working conditions, I manage to work safely and productively every morning shift.” The items will be scored on a 7-point scale ranging from 1 (completely disagree) to 7 (completely agree).

The other confounding and effect-modifying parameters that will be collected at baseline are as follows.

1. Sociodemographic variables: Information on age, gender, work unit, job title, and household composition will be collected.

2. Morningness-eveningness preferences: Personal morningness-eveningness preferences will be measured using 1 item based on the Morningness-Eveningness questionnaire [39].

3. Lifestyle: Physical activity and smoking behavior will be measured with 1 item each, based on the Study on Transitions in Employment, Ability, and Motivation cohort study [40].

4. Sleep patterns: Sleep disturbances will be measured using the Jenkins Sleep Questionnaire [41]. This questionnaire consists of the following 4 items: frequency in the difﬁculty of falling asleep in the previous month, difﬁculty sleeping continuously, waking up several times each night, and waking up feeling tired and worn out after the usual amount of sleep. The response alternatives range from 1 (not at all) to 6 (22-31 days).

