#### EMA

During the intervention period, all employees will also be asked to participate in the EMA. EMA is a method for self-monitoring through the collection of self-reports on indices of behavior, cognition, or emotions in near real time in the daily lives of the participants, often through digital devices [42-44]. The smartphone-based questionnaire app allows us to digitally collect daily life momentary assessments of changes in employees’ levels of fatigue and recovery behavior, in relation to momentary context and activity. As such, it provides insight into the short-term, within-person mechanisms linking fatigue and recovery with short-term intervention effects. Event-contingent data collection protocols will be used, indicating that data entry takes place when a predefined event occurs [45,46]. The predefined event in this study is the formal work break. Participants will be asked to fill the data in the EMA app for a period of 14 consecutive days (1) directly before taking a work break, (2) directly after taking a work break, and (3) directly after the end of their shift. Each measurement moment will take about 1-2 minutes. In alignment with organizational management, we chose a period of 14 days to ensure enough day-level data points (despite rotating shift schedules and possible dropouts) without overburdening the participants. The use of the intervention, however, can continue after data has been collected.

Table 1 shows the variables that will be measured. The information provided will give insight into the effectiveness of the different recovery strategies (eg, relaxation and activation) and the influence of work break control, shift types, and personal characteristics (eg, age, chronotype, job position) on recovery outcomes. The start of the 14-day EMA period will be communicated through (1) the app via prompts, (2) the manager of the specific unit, and (3) through communication at the workplace (eg, posters, newsletters).

**Table 1 table1:** Variables retrieved through EMA.

Variable	Items	Questionnaire	Before break	After break	After shift
Shift type	1	What shift are you working today?	✓		
Sleepiness	1	Karolinska Sleepiness Scale [47]: scored on a scale from 1 (extremely alert) to 10 (very sleepy, difficulty in staying awake)	✓	✓	✓
Stress	1	Self-developed: “How do you currently feel?” scored on a visual analog scale (ranging from “stressed” to “relaxed”)	✓	✓	✓

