### Statistical Analysis

First, intervention results will be analyzed by performing mixed model repeated measures analyses (multivariate analysis of variance; time*group interaction) on longitudinal survey data with the outcome measures at follow-up (T0-T1, T1-T2, and T0-T2 comparisons) as the dependent variables. Furthermore, the effectiveness of the intervention will be analyzed by applying multilevel analyses on data collected within the EMA study (before break-after break and before break-after shift comparisons). Data will be collected and analyzed at 3 levels: (1) day level, (2) employee level, and (3) work unit level. Dropouts will be documented and included in the data analysis to the point of dropout. Potential confounders or effect modifiers (eg, age, gender, chronotype) will be compared between the intervention and the waiting list control group by *t* tests for independent samples and chi-square tests. For all analyses, a two-tailed significance level of *P*<.05 will be applied. The multilevel analyses will be conducted using R and the mixed model repeated measures analyses will be performed using SPSS software (IBM Corp, Version 25.0). A detailed analysis plan will be developed prior to finalization of the dataset.

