### Study Limitations

From an occupational and epidemiological point of view, this study can be classified as a prevention-effectiveness study [27,55,56]. The characteristics of a prevention-effectiveness study design are as follows: small sample size, no randomization or blinding, and quantitative and qualitative measures. These characteristics ensure the internal validity of the study [55]. However, this type of study, as does ours, contains some limitations as well. First, because we do not use randomization, allocation bias could take place. However, in this study, it is impossible to randomly assign participants to an intervention and control group for practical and ethical reasons. Therefore, the waiting list control group principle was introduced. Moreover, one could argue that owing to the preallocation of the departments, the commitment of the management to the study is assured (ie, they know that an actual intervention is taking place and things have to be arranged to get this done), which enhances the feasibility of this study. A second limitation is the timeframe of the study. Behavioral and organizational changes do not occur easily or quickly. Therefore, the follow-up period (6 months) might be too soon to establish health-related effects. It might be, for instance, that changing recovery habits initially requires additional effort before it pays off in long-term reduced levels of fatigue. By combining quantitative data with qualitative data, we aim to gain further insight into this matter. A third limitation is that the evaluation of the effectiveness of the intervention fully relies on self-reported data. It would be interesting, for instance, to also assess fatigue levels through simple cognitive tests. For reasons of feasibility (ie, extensiveness of current research activities and accompanying time investment from the participants), we did not include such tests in the current design, but it might be a useful addition to the EMA method in the future studies. Another study limitation is the lack of generalizability of the findings. These study results may be organization-specific or sector-specific. However, workplace intervention studies for shift workers are still very scarce. The intervention in this study may therefore offer a starting point for future intervention studies in other organizations and sectors with shift work. Thereafter, aspects of the intervention should again be tailored to the workplace-specific context and target group through a participatory development and implementation process, as this has been argued to be a crucial condition for organizational interventions to be effective. An inevitable implication of this approach is that the effects have to be interpreted by considering unique contextual factors. A process evaluation will be performed to identify such contextual factors.

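### In the survey comparison of two non-randomised units, the only stated handling of the baseline confounders is low-powered significance testing; the time-by-group model names no covariates

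*Protocol article*

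**What the plan says.** The protocol article (Methods, Quasi-Experimental Field Study) states that "this study was designed as a quasi-experimental field study with a waiting list control group and pretest-posttest design". Which unit waits is not left to chance. Under Setting and Study Population: "This selection will be made in close consultation with the management, considering factors such as organizational planning, expected availability of time, and resources". The same section asserts, without figures, that "With respect to the demographics and the workload, the units are highly comparable". Study Limitations puts this first: "because we do not use randomization, allocation bias could take place".

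The Web-Based Survey section introduces the baseline variables with "The other confounding and effect-modifying parameters that will be collected at baseline are as follows". It then lists sociodemographics (including age, gender, job title and household composition), morningness-eveningness preference, physical activity, smoking and sleep disturbance.

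The Statistical Analysis section gives the survey model as "mixed model repeated measures analyses (multivariate analysis of variance; time*group interaction) on longitudinal survey data". Of the baseline variables it says "Potential confounders or effect modifiers (eg, age, gender, chronotype) will be compared between the intervention and the waiting list control group", by independent-samples t tests and chi-square tests. A two-tailed 5% level applies to all analyses. The section says nothing about what follows from a significant or a non-significant result. It closes by announcing a detailed analysis plan before the dataset is finalised.

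**The concern.** In a non-randomised comparison, measured confounders matter because they can be used in estimating the effect. Here the article names a procedure for them, and the procedure is a weak one in three respects.

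- A significance test of baseline balance mostly reflects sample size. At these numbers a non-significant result says little about balance.
- A significant result has no stated consequence for the survey model.
- The same between-unit tests are applied to effect modifiers. Whether a variable differs between units says nothing about whether the intervention effect varies with it; that needs an interaction with group and time.

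If the survey analysis were run as stated, the main between-unit contrast would carry any measured individual-level confounding of change, although the data to reduce it are being collected.

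**Working it through.** **Inputs from the article.** Expected 56 per unit (150 × 0.75 / 2 = 56.25); minimum 37 per group; Cohen f = 0.15; power 0.80; two-sided 5% level (Sample Size and Statistical Analysis sections).

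**Step 1: the plan's own figure.** For the repeated-measures group-by-time interaction with two groups, λ = f²·N·m/(1−ρ), df1 = m−1, df2 = (N−2)(m−1). The article states neither m nor ρ. Assuming m = 3 (T0, T1, T2) and ρ = 0.5, N = 74 gives λ = 0.0225 × 74 × 3 / 0.5 = 9.99 with 2 and 144 df, and power 0.806. The smallest N is 73, that is, 37 per group. The stated sample size reproduces and is not in question.

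**Step 2: what the balance tests can detect.** Two-sample t test, noncentrality δ = d·√(n/2), where d is the true difference in SD. At n = 56, for example, d = 0.3 gives δ = 0.3 × √28 = 1.59 against a critical value of 1.98.

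| True imbalance | Power, 56 per unit | Power, 37 per unit |
|---|---|---|
| 0.2 SD | 18% | 14% |
| 0.3 SD | 35% | 25% |
| 0.4 SD | 55% | 40% |
| 0.5 SD | 75% | 56% |

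The smallest observed difference that can reach P<.05 is t·√(2/n): 1.98 × √(2/56) = 0.37 SD at 56 per unit, and 1.99 × √(2/37) = 0.46 SD at 37. For a binary factor of 30% against 45%, power is 37% and 26% respectively.

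**Step 3: what such an imbalance could do.** A covariate with a constant effect on the outcome cancels from the change between time points. The bias in the between-unit difference in change is therefore imbalance × r, where r is the within-unit correlation of the covariate with change. Neither quantity is in the article; both are assumptions.

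- Imbalance 0.3 SD, r = 0.1: 0.3 × 0.1 = 0.03 SD
- Imbalance 0.3 SD, r = 0.3: 0.3 × 0.3 = 0.09 SD
- Imbalance 0.3 SD, r = 0.5: 0.3 × 0.5 = 0.15 SD

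**Step 4: against the planned effect.** What f = 0.15 means in SD depends on how it is read. As d = 2f it is 0.30 SD. As a two-measurement interaction with ρ = 0.5, λ = 0.0225 × N × 2 / 0.5 = 0.09N. Setting this equal to the t-test value d²N/4 gives d² = 0.36 and d = 0.60 SD. The mid-range bias of 0.09 SD is then 0.09/0.30 = 30% or 0.09/0.60 = 15% of the planned effect.

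**Step 5: cost of adjusting.** With q covariates, df2 becomes (N−2−q)(m−1) and λ is multiplied by 1−R², where R² is that of group on the covariates. Take N = 112, m = 3, ρ = 0.5, and assume q = 8.

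- Unadjusted: λ = 15.12, power 0.943
- R² = 0.10: λ = 13.61, power 0.917
- R² = 0.20: λ = 12.10, power 0.881

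The n for 80% power rises from 37 to 41 or 46 per group, below the expected 56. For the T0–T1 contrast alone (m = 2, other assumptions unchanged), λ is 10.08, 9.07 and 8.06, and power is 0.88, 0.85 and 0.80. None of this credits any precision gained from prognostic covariates.

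**The case against.** A reader might infer that the confounders will never enter an effect model and that imbalance will be left unadjusted. The article does not say so. It is silent on survey covariates, it is a condensed account, and a detailed analysis plan is announced. That objection stands, and the point is limited to what the article states. The announcement does not, however, withdraw the method that is named.

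It might also be inferred that testing is the variables' only use anywhere. That is not so: the EMA section intends to examine "the influence of work break control, shift types, and personal characteristics (eg, age, chronotype, job position) on recovery outcomes". That concerns the momentary data and does not adjust the survey comparison of units.

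The time-by-group contrast includes T0, so baseline differences in outcome and time-constant effects of age, gender or chronotype drop out. This stands and narrows the risk to variables related to change.

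The article does not claim that a non-significant test proves balance or that the tests decide adjustment. That is also fair: the weakness is that no use of the results is stated. The claimed comparability of the units is some reassurance, but it is qualitative and covers only demographics and workload.

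Finally, a reader might set the 0.09 SD bias against a 0.2 SD effect and conclude that nearly half the effect is at risk. The 0.2 SD benchmark is not in the article, and f = 0.15 supports a share of about 15% to 30%.

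**Conclusion.** The point holds for the survey comparison. The only stated handling of measured confounders is a set of tests that miss a 0.3 SD imbalance about 65% of the time at 56 per unit and cannot address effect modification, beside a model that names no covariates. The exposure is measured confounding of change. Its illustrative size is 0.03 to 0.15 SD, which rests on an assumed 0.3 SD imbalance and assumed correlations with change of 0.1 to 0.5. The documents do not show that such an imbalance exists, nor that adjustment has been ruled out. This is a worthwhile and inexpensive improvement to the analysis; it does not show that the result will be wrong.

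**What to change.** In the announced analysis plan, or in the Statistical Analysis text:

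1. Replace the between-unit t and chi-square tests with standardised differences for every baseline variable.
2. Adjust the survey effect for a short list of variables already collected, chosen on substantive grounds before analysis and used whatever the balance shows; for example age, job title, chronotype and baseline sleep disturbance.
3. Enter each as a covariate-by-time term. A main effect alone does not adjust the time-by-group contrast.
4. Report the unadjusted estimate alongside.
5. If effect modification is examined, use covariate-by-group-by-time terms and label them exploratory, because power for them is low at this size.
6. State that with one unit per condition, individual-level adjustment cannot remove confounding at unit level, such as management decisions or events affecting one unit only.

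No new data are needed. The cost is a few degrees of freedom and a small loss of power: from about 0.94 to 0.88–0.92 at 56 per unit over three measurements, with ρ = 0.5, eight covariates and R² of 0.10 to 0.20 assumed. A shorter list costs less: with three covariates and R² = 0.05, power is 0.93. Exploratory three-way terms would use further degrees of freedom, so they belong in separate models.

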### Sample Size

The sample size calculation is based on finding an effect on the need for recovery. This variable was chosen because of its test-retest reliability and sensitivity to detect change, indicating that the need for recovery may be a useful tool for evaluating interventions related to occupational health [34]. Based on previous studies [47,51], a small effect size is expected. Power calculations indicate that to detect a small effect in the context of a repeated measurements analysis of variance (Cohen *f*=0.15), at least 37 subjects are necessary in each study group (power=0.80 and α=.05), and calculations were performed using G*power [52]. The response rates of similar PAR studies have been shown to be around 75% or higher [31,32]. Given the intended sample size of 150 subjects and the expected response rate of 75%, resulting in 56 subjects per group, the study has sufficient power to even detect slightly smaller effects [53].

## Results

This study is supported by the Netherlands Organization for Applied Scientific Research Work and Health Research Program, which is funded by the Ministry of Economic Affairs and supported by the Dutch Ministry of Social Affairs and Employment, program number 19.204.1-3. This study was approved by the institutional review board on February 7, 2019. From June to August 2019, baseline data were collected, and from November to December 2019, the first follow-up data were collected. The second follow-up data collection and data analysis are planned for the first two quarters of 2020. Dissemination of the results is planned for the last two quarters of 2020.

## Discussion

### Principal Aspects of This Study

Shift work (ie, irregular working hours) can cause negative short-term effects for both employees and employers, such as increased fatigue levels, concentration problems, and consequently, an augmented risk of accidents and productivity loss. Unfortunately, evidence-based interventions to mitigate the negative effects of shift work are still lacking. Previous research studies have shown that a possible way to counteract the negative short-term effects of shift work is by enhancing the recovery of the employees during work. Therefore, the aim of this study is to develop, implement, and evaluate an intervention focused on enhancing the recovery of shift workers during working hours.

### Study Strengths

The design of this study has several strengths. First, by making use of the PAR approach, stakeholders at all levels of the company are involved. This bottom-up involvement of the stakeholders will contribute to the commitment to the proposed interventions, which will likely translate into better overall intervention adherence and compliance. Moreover, it allows the target group to participate in the development and implementation of the intervention. This approach will stimulate problem ownership and commitment at all levels of the organization and has the potential to contribute to organizational sustainability [29], for which the interventions are more likely to have the proposed impact [28]. Another strength of the study design is that the timeline for the experimental unit allows us to compare the short-term intervention effects (T1) with the long-term effects (T2). In addition, the intervention development is conducted in a similar way in both the departments, but the eventual workplace interventions can differ. As a consequence, we can compare different solutions on similar proposed outcomes, further contributing to both theory and evidence-based practice [54]. In addition, to determine the effects of the workplace intervention, we use a rather unique data triangulation. Next to group-level outcome measurements with a web-based questionnaire, EMA measurements are used to gain insight into the working mechanisms of the intervention and to determine the influence of the type of recovery strategy chosen, the time of day, the type of shift, and intraindividual differences. Moreover, a process evaluation will be performed in order to gain more insight into what aspects of the intervention work for whom and why [48]. The process evaluation outcomes are assessed qualitatively (ie, group interviews, observations, data logs) and quantitatively (ie, self-reported measures in digital surveys) and whenever possible, complemented with objective organizational data (eg, sickness absence registration).

